### **5.3 Accountability procedures for study drugs**

Upon receipt of the study drugs from the sponsor, investigator or designated individual at each study site should sign a “Receipt form of study drugs” to ensure that the information on the packing slip matches exactly with what has been sent to the site, including the amount, lot numbers and quantity. When an eligible subject is included, investigator or designated individual will dispense the proper drugs in strict accordance with the randomization list. Each time a study drug is dispensed, there should be a “Drug dispensing form” as to the amount dispensed, to whom it is dispensed, and the date and signature of the person dispensing the drug.

Subjects should be advised to return all unused drugs at each study visit. Study personnel should record the amount (number of capsules) and date of return. Study drug will be properly accounted for and tracked with adequate documentation so as to assess subject's compliance.

The study drugs should be stored in a dry and ventilated place at room temperature.

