### 3.5 Blinding

Since the dosage forms of XXK capsule and CDS tablet are different, dummy preparations in both capsule and tablet forms are prepared to allow for double-blind and double-dummy comparison.

Blinding is conducted in two steps in this trial, i.e. treatment is randomly assigned to patients in the first step, and then A or B is randomly assigned to the treatment in the second step. The randomization lists of the two blinding steps are kept in sealed envelopes in duplicate, one stored at the clinical study office of China Academy of Chinese Medical Sciences and the other kept by the sponsor.

Two-step unblinding will be performed after all patients have completed the trial. Step 1: after all data is locked, personnel who keeps the sealed envelop will assign A or B to either of the treatments for the conduct of statistical analysis and production of statistical reports. Step 2: after the statistical analysis is finished and the clinical trial report is prepared, the corresponding treatment that A or B refers to will be unblinded.

An emergency envelope will also be provided along with each test drug in its package, which should only be opened in case of emergency unblinding.

A patient's treatment assignment should only be unblinded when knowledge of the treatment is essential for the further management of the patient.

If the identity of the test medication is necessary for patient management (in the case of a serious complication or a serious adverse event), emergency unblinding is permitted. Investigator, project manager, and clinical study coordinators should participate in the process of emergency unblinding; when, where and why the unblinding occurs as well as each personnel's signature should also be documented. The principal investigators should make every attempt to contact the sponsor after blinding.

At the time of emergency unblinding, it is also necessary to ensure that adequate procedures are in place to ensure the integrity of the data.

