#### **4.5.3 Withdrawal/dropout criteria**

- Those who did not fulfill the eligibility criteria but were included by mistake;
- Those who fulfilled the eligibility criteria but did not take any study drug after randomization;
- Those with poor compliance that might interfere with the efficacy and safety evaluation;

- Those who experienced serious AEs, complications or special physiological changes, making it inappropriate to continue with the trial;
- Individual cases that were unblinded prematurely;
- Those who discontinued the trial voluntarily;
- Those who used any disallowed concomitant medication, especially those that had an obvious effect on the study drug and might interfere with the efficacy and safety evaluation;
- Those who discontinued or lost to follow-up for any other reasons or died during the trial;
- Those with incomplete data that might interfere with the efficacy and safety evaluation.

For all withdrawal/dropout cases, the potential reasons must be recorded. Patients who experienced any AE during the trial must be included in the statistical analysis of adverse drug reactions. Those who have taken the study drug for at least 1 week should be included in the statistical analysis of drug efficacy.

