### **5.4 Study treatment**

#### **5.4.1 Drug administration**

(1) trial group: XXK capsule + placebo of CDS tablet, oral, 2 capsules + 2 tablets a time, 3 times a day;

(2) control group: CDS tablet + placebo of XXK capsule, oral, 2 tablets + 2 capsules a time, 3 times a day.

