## **11 STATISTICAL CONSIDERATIONS AND ANALYTICAL PLAN**

### **11.1 Selection of data sets**

#### **11.1.1 Efficacy analysis sets**

Full analysis set (FAS): includes all randomized patients and those without any evaluable follow-up data after randomization are excluded. For patients who did not complete the study according to the protocol, a last observation carried forward (LOCF) procedure was performed.

Per protocol set (PPS): includes all subjects in the FAS population who meet the study treatment compliance criteria and had no major protocol violations.

For primary outcome measures, statistical analyses will be performed separately in both FAS and PPS populations.

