### **12.3 Compliance enhancement**

The informed consent procedure is essential to ensure patients' compliance to treatment. The study drug, laboratory examinations, transportation and healthcare consultation will be provided by the sponsor free of charge.

Compliance rate is calculated by taking the amount of drug ingested divided by the amount the patient should have ingested and multiply by 100%. A compliance rate at 80%-120% defines good compliance; while that < 80% or > 120% defines poor compliance.

Patients should be asked to report all the concomitant medications while on study. Patients who have poor efficacy or poor compliance should be closely followed up.

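### Section 5.3 names only capsules for the count of returned drug, and section 12.3 names no dosage form, so compliance with the active control tablet is not secured for entry to the per protocol set

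*Protocol*

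**What the plan says.** Section 3.5 sets up the double-dummy: "dummy preparations in both capsule and tablet forms are prepared to allow for double-blind and double-dummy comparison". Section 5.4.1 gives the control regimen as "CDS tablet + placebo of XXK capsule, oral, 2 tablets + 2 capsules a time, 3 times a day". The XXK arm takes the same numbers, with the roles of active drug and placebo exchanged.

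Section 5.3 has patients bring back everything unused at each visit and tells staff what to write down: "Study personnel should record the amount (number of capsules) and date of return". It gives assessment of compliance as the purpose of drug accountability.

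Section 12.3 turns this into a rate: "Compliance rate is calculated by taking the amount of drug ingested divided by the amount the patient should have ingested", expressed as a percentage. It adds that "A compliance rate at 80%-120% defines good compliance" and that values outside the window are poor compliance. Neither capsule nor tablet is mentioned there.

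Section 11.1.1 makes the rate a condition for the PPS, which "includes all subjects in the FAS population who meet the study treatment compliance criteria" and had no major protocol violations. For the primary outcomes, "statistical analyses will be performed separately in both FAS and PPS populations".

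**The concern.** The one unit named for the return count is the active product in one arm and the placebo in the other. If site staff follow section 5.3 to the letter, the 80% limit does its job in the XXK arm. In the control arm it measures how well patients took their dummy capsules. Control patients who missed the active tablets could stay in the PPS, and control patients who took every active tablet but missed placebo capsules could be removed.

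The primary outcomes are analysed in the PPS as well as in the full analysis set (FAS), so a PPS rule that works differently by arm weakens the PPS as a supporting analysis in a superiority trial. The gap also arises at data capture. A statistical analysis plan can choose a formula later, but it cannot recover tablets that nobody counted at the visit.

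**Working it through.** The protocol states no figure on this point that could be reproduced. The check applies its compliance formula to its regimen.

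**Inputs**
- Dose: 2 capsules and 2 tablets, 3 times a day (5.4.1).
- Duration: 20 weeks = 140 days (5.4.2).
- Rate: amount ingested / amount due × 100%; good compliance is 80%-120% (12.3).

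**Amount due per patient**
- Capsules: 2 × 3 × 140 = 840. Tablets: 2 × 3 × 140 = 840.
- 80% of one form: 0.80 × 840 = 672 units.
- 80% of both forms pooled: 0.80 × 1,680 = 1,344 units.

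**Reading 1: capsules only, as 5.3 is worded**
- Control patient, 840 capsules and 0 tablets: 840/840 = 100%. Meets the criterion with 0% of the active drug.
- Control patient, 840 tablets and 663 capsules: 663/840 = 78.9%. Fails, with 100% of the active drug.
- XXK patient, 840 tablets and 0 capsules: 0/840 = 0%. Fails, correctly.

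The rule therefore makes two kinds of error in the control arm, wrong inclusion and wrong exclusion. In the XXK arm the count does follow the active drug.

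**Reading 2: both forms pooled**
- All 840 placebo units taken: the patient passes with 1,344 − 840 = 504 active units, and 504/840 = 60%.
- All of one form and none of the other: 840/1,680 = 50%. Fails.

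This rule is the same in both arms, but it lets through a patient well below 80% of the active drug. The 60% assumes that placebo intake does not exceed the amount due.

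**Reading 3: each form counted and each held to 80%-120%**
- 840 capsules and 0 tablets: 100% and 0%. Fails in either arm.
- 840 placebo units and 504 active units: 100% and 60%. Fails in either arm.

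Only Reading 3 guarantees at least 80% of the active drug for every patient who meets the compliance criterion. The protocol does not call for it.

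**The case against.** The parenthesis in 5.3 may be shorthand. The same section has all unused study drug returned and properly accounted for, and 12.3 speaks of drug ingested without limiting it to capsules. The label text in section 5.2 also describes only capsule dosing, although tablets are supplied too, so capsule-centred wording looks like a habit of the document. The return form and the case report form are not shown and may have a field for tablets. All of this stands. A reader might infer that tablets went uncounted and that control compliance was in fact measured on placebo. The protocol does not say so; it only fails to name tablets.

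A reader might also infer a bias towards XXK of some definite size in the primary result. The documents do not support that:
- They give no rate at which patients take one form and skip the other. Both forms are taken together under blinding, so patients have no allocation-based reason to skip only one.
- Any tilt towards XXK needs the capsule-only reading and some real effect of CDS. Under pooling the rule treats both arms alike.
- Membership of the FAS does not depend on compliance.
- Section 4.5.3 lists as a withdrawal ground "Those with poor compliance that might interfere with the efficacy and safety evaluation". That is a judgement about interference, not the capsule count, so it does not show that the count reaches the FAS.

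It can further be said that whether to pool the forms is a detail for the statistical analysis plan. That holds for the formula. It does not hold for which units staff count at the visit, and that is where 5.3 gives a written instruction that omits the active control product.

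**Conclusion.** The point holds as a defect of wording with a possible practical consequence. As written, sections 5.3 and 12.3 do not secure that control patients in the PPS took the active tablet. The literal reading gives an arm-asymmetric rule: 100% compliance with no active drug at one extreme, and exclusion at about 79% of placebo capsules despite full active dosing at the other. The pooled reading is symmetric but passes 60% of the active drug.

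The effect is on PPS membership. It is probably small, because it needs patients who take the two forms to clearly different degrees, and the protocol gives no basis for estimating how many there are. No shift in the treatment difference can be calculated. The conclusion assumes that no form outside the protocol already requires a tablet count; if one does, what remains is to state the rate per form in 12.3. Minor severity, and a cheap improvement.

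**What to change.** In 5.3, have staff record the number of capsules and the number of tablets returned, with the date. In 12.3, calculate compliance separately for capsules and for tablets, and define good compliance as 80%-120% for both forms. Apply the same rule in both arms, so that nobody needs to know which form is active and blinding is untouched.

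The cost is one extra count per visit and an added sentence in 12.3; no new visit is needed. The PPS may become slightly smaller, because two limits must be met instead of one.

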### **5.4 Study treatment**

#### **5.4.1 Drug administration**

(1) trial group: XXK capsule + placebo of CDS tablet, oral, 2 capsules + 2 tablets a time, 3 times a day;

(2) control group: CDS tablet + placebo of XXK capsule, oral, 2 tablets + 2 capsules a time, 3 times a day.

#### 5.4.2 Duration

20 weeks treatment.

#### 5.4.3 Concomitant medications

- Sublingual nitroglycerin is permitted if necessary, also with detailed documentation;
- Other TCM or WM medications targeting the treatment of angina or CHD will be disallowed during the trial;
- If other medication or therapy is required to treat the concomitant diseases, then the name of the drug or therapy, actual dosage, dosing frequency and start/stop time should be well-documented.

## 6 OBSERVATION INFORMATION

### 6.1 Safety parameters

- Vital signs;
- Blood, urine and stool routine tests;
- Liver function (ALT), kidney function (BUN and Cr);
- Any AE that occurs throughout the treatment period.

The first 3 items will be observed or evaluated before and after treatment.

### 6.2 Efficacy parameters

The primary efficacy endpoint of this study is:

- Proportions of patients who were angina-free.

Angina-free was defined as the responses of patients' anginal symptoms were "none" on the Quantification Score of Angina Pectoris (see page 19 for details) including three dimensions (attack frequency, severity and duration of angina) over the 20-weeks treatment phase. The Quantification Score of Angina Pectoris comprising questions investigating the patients' anginal symptoms was administered by the physician in charge of the study at 2, 4, 6, 8 and 20 weeks in each center.

- Proportion of effective electrocardiogram (ECG) improvement.

The effective ECG improvement was defined as a standard 12-lead ECG returns to normal(or within the normal range) according to the International Society and Federation of Cardiology/World Health Organization after 20-weeks long term treatment. The ECG was performed at 0,8, and 20 weeks during treatment.

Secondary efficacy endpoints are:

- Change from baseline in weekly average frequency of self-reported angina episode over the 20-weeks treatment phase.
- Weekly average nitroglycerin consumption rate at week 8 and week 20.

Throughout the study, patients recorded the occurrence of anginal attacks and the number of nitroglycerin use on diary cards and the study staff at each clinical site reviewed the angina and nitroglycerin use cards with the patient at each study visit(2, 4, 6, 8 and 20 weeks) to ensure accuracy.

- Change from baseline in 5 dimensions of the Seattle Angina Questionnaire (SAQ) and the proportions of patients who were clinical significance at week 8 and week 20.

The SAQ is a disease-specific functional status measure that was developed to quantify the physical and emotional effects of CAD[6].Each SAQ dimension (anginal frequency, physical limitation, anginal stability, disease perception, and treatment satisfaction) was scored on a scale of 0 to 100 and the clinical significance was defined as a difference of 8 points or more on the physical-limitation scale, 25 or more on the angina-stability scale, 20 or more on the angina-frequency scale, 12 or more on the treatment-satisfaction scale, and 16 or more on the quality-of-life scale[7].Patients will complete the SAQ at 0,8, and 20 weeks.

- Change from baseline in the blood stasis syndrome and the proportion of patients who had significant syndrome improvement.

Blood stasis syndrome which a common syndrome of chronic stable angina in TCM including the following symptoms: angina, choking sensation in the chest, palpitation, dark purple lips, ecchymosis on the tongue, and fine-choppy pulse.The syndrome score was assessed by using the Quantification score of TCM syndrome(with higher scores indicating higher severity, see page20 for details)and administered by the physician in charge of the study at 2, 4, 6, 8 and 20 weeks in each center.

The significant syndrome improvements defined as clinical signs and symptoms have been greatly improved, and decrease in syndrome score  $\geq 70\%$ [3].

- Change from baseline in ECG exercise test (the first 1/3 of patients included at each site) performed at 0 and 8 weeks.

Investigators should be aware of the contraindications to exercise test, and patients should be closely monitored during the test to ensure his/her safety, including ECG, BP, and angina.

- Change from baseline in serum lipid: total cholesterol, triglyceride, HDL cholesterol, and LDL cholesterol, measured at 0 and 8 weeks during treatment.
- Related signs: heart rate, rhythm, murmur, and BP, recorded before and after Treatment.
- Accompanying symptoms after treatment: fatigue, shortness of breath, aversion to cold, cold extremities and etc. (recorded as “yes” or “no”).

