### OUTCOME MEASURES:

Efficacy:

---

---

The primary efficacy endpoint of this study is:

- Proportions of patients who were angina-free.
- Proportion of effective electrocardiogram (ECG) improvement.

Secondary efficacy endpoints are:

- Change from baseline in weekly average frequency of self-reported angina episode over the 20-weeks treatment phase.
- Weekly average nitroglycerin consumption rate at week 8 and week 20.
- Change from baseline in 5 dimensions of the Seattle Angina Questionnaire (SAQ)

and the proportions of patients who were clinical significance at week 8 and week 20.

- Change from baseline in the blood stasis syndrome and the proportion of patients who had significant syndrome improvement.
- Change from baseline in ECG exercise test (the first 1/3 of patients included at each site) performed at 0 and 8 weeks.
- Change from baseline in serum lipid: total cholesterol, triglyceride, HDL cholesterol, and LDL cholesterol, measured at 0 and 8 weeks.
- Related signs: heart rate, rhythm, murmur, and BP, recorded before and after

Treatment.

- Accompanying symptoms after treatment: fatigue, shortness of breath, aversion to cold, cold extremities and etc. (recorded as “yes” or “no”).

Safety:

- Vital signs;
  - Blood, urine and stool routine tests;
  - Liver function (ALT), kidney function (BUN and Cr);
  - Any AE that occurs throughout the treatment period.
-

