## 4.5 Eligibility criteria

#### **4.5.1 Inclusion criteria**

- Patients who fulfill the diagnostic criteria of stable angina pectoris;
- Patients who fulfill the diagnostic criteria of CCS grading class I , II or III;
- Patients who fulfill the diagnostic criteria of blood stasis syndrome;
- Patients who have angina attacks  $\geq 2$  episodes per week;
- Ischemic changes on ECG: ST segment depression  $\geq 0.05\text{mv}$  and/or deep T wave inversions  $> 0.2\text{mv}$ , flat T wave less than  $1/10R$ , or positive exercise stress test.
- Aged 40-70 years.
- Those who are willing to provide a signed informed consent form.

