#### **11.2 Dynamic statistical plan**

One interim analyses will be conducted under blinding conditions after 1/2 of the total number of cases have completed the trial.

Statisticians and principal investigators are responsible for drafting a written plan for statistical analysis according to the study protocol. It includes the number of included, excluded or withdrawal patients, the demographic and baseline characteristics of included patients, treatment compliance, efficacy analysis and safety analysis.

Qualitative data will be described with absolute and relative (proportion or percentage) values; and quantitative data will be summarized with mean, standard deviation, maximum, minimum, and median.

Paired t-test will be used for comparison before and after treatment within a treatment group. In analysis of variance (ANOVA) for multiple comparisons within a group, if the variances are assumed to be equal, then Student-Newman-Keuls (SNK) significance test will be used for pairwise comparison; if the variances are not assumed to be equal, then non-parametric test will be applied. Two-samples t-test will be used for comparison between treatment groups. Fourfold table will be displayed for comparison of categorical parameters: Chi-squared test for nominal categorical data and rank sum test for ordinal categorical data. Also, the analysis of covariance (ANCOVA) can be used to control for potential confounding variables.

All *P* values are two-side. Statistical significant level is set to be 0.05.

For between-group comparisons, chi-square test, Fisher's exact test, Wilcoxon rank test or Cochran-Mantel-Haenszel (CMH)  $\chi^2$  test may be used for qualitative data; while t-test, ANOVA, Wilcoxon rank test or ANCOVA may be applied for quantitative data.

**Baseline analysis:** Demographic and baseline characteristics will be reported for each subject. Comparisons between the treatment groups will be conducted using ANOVA or

Chi-square test to assess the degree to which comparability of randomization can be achieved.

**Dropout analysis:** The overall dropout rate and the dropout rate due to AEs will be compared between the treatment groups by using Chi-square test.

**Efficacy analysis:** The effect of different study sites on efficacy parameters will be considered and analyzed.

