## 15 CLINICAL TRIAL FLOWCHART

Clinical Trial Flowchart

| Stages                             | Recruitment                     | Treatment Phase |        |        |        |         |
|------------------------------------|---------------------------------|-----------------|--------|--------|--------|---------|
| Visits                             | 1st                             | 2nd             | 3rd    | 4th    | 5th    | 6th     |
| Time                               | Before
treatment
(Week 0) | Week 2          | Week 4 | Week 6 | Week 8 | Week 20 |
| Informed consent                   | √                               |                 |        |        |        |         |
| Medical history                    | √                               |                 |        |        |        |         |
| Eligibility criteria               | √                               |                 |        |        |        |         |
| Randomization                      | √                               |                 |        |        |        |         |
| Drug distribution                  | √                               | √               | √      | √      | √      | √       |
| Patient general
characteristics | √                               |                 |        |        |        |         |
| Specialty examination              | √                               | √               | √      | √      | √      | √       |
| TCM syndrome scoring               | √                               | √               | √      | √      | √      | √       |
| Blood routine                      | √                               |                 |        |        | √      | √       |
| Urine routine                      | √                               |                 |        |        | √      | √       |
| Stool routine                      | √                               |                 |        |        | √      | √       |
| Liver function                     | √                               |                 |        |        | √      | √       |
| Kidney function                    | √                               |                 |        |        | √      | √       |
| Blood lipid                        | √                               |                 |        |        | √      |         |

|                                               |   |   |   |   |   |   |

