|-----------------------------------------------|---|---|---|---|---|---|
| ECG                                           | √ |   |   |   | √ | √ |
| Recording of concomitant medication           | √ | √ | √ | √ | √ | √ |
| Recording of AEs                              |   | √ | √ | √ | √ | √ |
| Quantification Score of Angina Pectoris       | √ | √ | √ | √ | √ | √ |
| Seattle Angina Questionnaire(SAQ)             | √ |   |   |   | √ | √ |
| Review of angina frequency, nitroglycerin use | √ | √ | √ | √ | √ | √ |
| ECG exercise test                             | √ |   |   |   | √ |   |

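### Baseline angina frequency has no stated source or look-back window, so the within-arm paired test of its change can be significant with no treatment effect; the between-arm comparison stays valid but should be baseline-adjusted

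*Protocol*

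**What the plan says.** - **Endpoint.** The synopsis and 6.2 list as a secondary endpoint "Change from baseline in weekly average frequency of self-reported angina episode over the 20-weeks treatment phase".
- **On-treatment source.** Section 6.2: "Throughout the study, patients recorded the occurrence of anginal attacks and the number of nitroglycerin use on diary cards". Staff then "reviewed the angina and nitroglycerin use cards with the patient at each study visit(2, 4, 6, 8 and 20 weeks) to ensure accuracy".
- **Week 0.** The flowchart (Section 15) ticks consent, eligibility, randomisation and "Drug distribution" in a single pre-treatment column headed Week 0. No earlier visit or run-in is shown. The row "Review of angina frequency, nitroglycerin use" is ticked at all six visits, Week 0 included.
- **Entry.** Section 4.5.1 admits "Patients who have angina attacks" at a rate of 2 or more episodes per week. The period and record on which this is judged are not stated.
- **Tests.** Section 11.2: "Paired t-test will be used for comparison before and after treatment within a treatment group". Between arms it names a two-sample t-test and allows ANCOVA as an option. All tests are two-sided at 0.05.
- **Nitroglycerin.** The secondary endpoint is "Weekly average nitroglycerin consumption rate at week 8 and week 20", which is a level. Only the categories in 7.6 (complete withdrawal, at least 50% fewer doses) need a pre-treatment value.

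**The concern.** A change score needs both halves measured in a comparable way. Here one half is a prospective diary count over 20 weeks. The other is a Week 0 value of unstated origin, taken at the visit where the patient qualifies on that same variable. Two mechanisms can then move the within-arm mean without any drug effect:

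- **Regression to the mean.** Patients are admitted because their reported frequency was at or above a threshold. Some were above it by chance and will later record fewer attacks.
- **A switch of instrument.** If the baseline is reported differently from the diary, the difference in method enters the change directly, in either direction.

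A paired t-test cannot separate either mechanism from treatment. This matters because the comparator is active (3.4) and there is no placebo arm, so a significant within-arm fall could easily be read as evidence that either product works. A second, smaller cost falls on the valid comparison: subtracting a noisy baseline adds variance that covariate adjustment would remove.

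**Working it through.** The protocol gives no mean, SD or expected change for weekly angina frequency, so it has no figure of its own to reproduce. The check has two parts.

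**1. What the visit structure allows.** Consent and the first drug supply share the Week 0 visit. A trial diary would not ordinarily start before consent, so no trial-diary baseline is described. The Week 0 tick shows that some baseline value is taken, but not from what record or over what period.

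**2. Null simulation: no treatment effect in either arm.**

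Inputs from the protocol: 368 patients per arm (736 / 2), entry at 2 or more attacks per week, 20 weeks of diary, two-sided 0.05.

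Inputs assumed: mean true rate 3, 5 or 7 per week; between-patient CV 0.5 or 0.8; baseline look-back 1 or 4 weeks; baseline reported at 0.8, 1.0 or 1.2 times the true rate. That makes 3 × 2 × 2 × 3 = 36 scenarios, with 1,000 runs each.

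Model: patient rate λ ~ Gamma; baseline B = Poisson(λ × weeks × reporting factor) / weeks, kept if B ≥ 2; diary rate Y = Poisson(20λ) / 20; change D = Y − B.

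| Baseline reporting | Look-back | Mean change per week | Paired test: improvement | Paired test: worsening |
|---|---|---|---|---|
| Unbiased | 1 week | −0.14 to −0.55 | 18% to 100% | 0% |
| Unbiased | 4 weeks | −0.03 to −0.18 | 5% to 93% | 0% to 1% |
| 20% too high | either | −0.80 to −1.75 | about 100% | 0% |
| 20% too low | either | +0.01 to +1.60 | 0% to 1% | 3% to 100% |

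A hand check of the two unbiased extremes uses z = mean change / (SD / √368):
- Mean 3, CV 0.5, 1 week: SD of change 1.72, standard error 1.72 / 19.18 = 0.090, z = −0.55 / 0.090 = −6.1. Rejection is near certain.
- Mean 7, CV 0.5, 4 weeks: SD 1.46, standard error 0.076, z = −0.03 / 0.076 = −0.4. Rejection stays near the nominal rate.

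**Between arms.** The two-sample t-test on D rejected in 4.0% to 6.3% of runs across all 36 scenarios. Simulation error around 5% is 1.96 × √(0.05 × 0.95 / 1,000) = 1.4 points, so this is consistent with nominal.

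**Noise in the change score, unbiased reporting.** Compare Var(D) with the residual variance after adjustment, Var(Y)(1 − ρ²), where ρ is the correlation of B and Y among those enrolled:
- Mean 3, CV 0.5, 1 week: Var(D) = 2.97; residual = 2.38 × (1 − 0.316) = 1.63; ratio 1.82.
- Mean 7, CV 0.8, 4 weeks: Var(D) = 2.40; residual = 30.38 × (1 − 0.9239) = 2.31; ratio 1.04.

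The change score thus carries about 4% more variance at one end and 81% to 84% at the other, depending on the simulation run. Ignoring the baseline altogether was usually noisier than the change score, so the covariate should be kept.

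**Change or level makes no difference once adjusted.** Y − B = a + τT + βB + e is the same model as Y = a + τT + (β + 1)B + e, so τ is identical.

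**The case against.** The strongest reply is that much of this is inferred. Section 6.2 has the diary running for the whole study, and the flowchart ticks a review at Week 0. The missing Week 0 in the list of card reviews proves little: 6.2 omits it in the same way for the angina score and the syndrome score, both of which the flowchart ticks at Week 0. The paired test is one general sentence, not tied to this endpoint, and no efficacy decision depends on it. The efficacy objectives in Section 2 are comparisons with CDS, and 11.2 already allows ANCOVA. A separate analysis plan may say more.

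Most of that stands, and it rules out three stronger readings that a reader might draw:

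- *Both arms must appear to improve.* The documents do not support this. They never say that the baseline is recalled. With a four-week window and unbiased reporting, false improvement can be as low as 5%; if baseline is under-reported, the apparent change is a worsening.
- *The randomised comparison is biased.* It is not. Both arms share the same baseline method under randomisation and blinding.
- *The nitroglycerin endpoint has the same fault.* It is a level at two time points. It is touched only through the 7.6 categories and any paired test of its use.

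What the reply does not remove: no pre-treatment diary period is described, the baseline has no stated source or window, entry is thresholded on the same variable, and the protocol prescribes a within-arm significance test while leaving baseline adjustment optional.

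**Conclusion.** The point holds in a limited form and is minor: it concerns one secondary endpoint. A within-arm paired P value for change in weekly angina frequency cannot be read as evidence of efficacy, because it can be significant under no effect: usually as apparent improvement, from the entry threshold or over-reporting, and as apparent worsening if baseline is under-reported. How often depends on attack rates, look-back and reporting bias, all of them assumed here because the protocol gives none. The between-arm comparison keeps its type I error. Its avoidable loss is the extra variance of unadjusted change scores, and that range applies to unbiased baseline reporting only. The angina-free primary endpoint rests on the physician-administered score, uses neither the diary nor a change from baseline, and is unaffected.

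**What to change.** - **Section 11.2, between arms.** Name as the analysis of this endpoint an ANCOVA of the on-treatment weekly diary rate (or, equivalently, the change) with Week 0 frequency as covariate, in place of the unadjusted two-sample t-test. The endpoint itself need not be redefined.
- **Section 11.2, within arms.** Report changes in angina frequency and nitroglycerin use descriptively, without P values and not as evidence of efficacy.
- **Section 6.2 and flowchart.** State the source and look-back window of the Week 0 frequency, and reconcile the Week 0 tick with the visit list in 6.2. Describe the value as it was actually obtained; do not label it as recall unless it was.

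The data collected stay the same. The cost is a wording amendment through the approval route in Section 18, dated as made after the interim analysis that 3.2 reports. The small downside is losing statements of significant improvement within an arm.
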